## Background

Perinatal asphyxia (PA), more appropriately known as hypoxic-ischemic encephalopathy (HIE), is a condition characterized by clinical and laboratory evidence of acute or sub-acute brain injury resulting from systemic hypoxemia and/or reduced cerebral blood flow [1]. The insult to the brain can occur in-utero, intrapartum or postnatally. Hypoxic-Ischemic Encephalopathy is the commonest etiology for neonatal encephalopathies and accounts for 23% of all term newborn deaths worldwide [2]. Severe HIE occur in 0.1–0.3% of births in resource-rich countries [2, 3]. However, the incidence of HIE is greater in low and middle-income countries (LMICs) [4] occurring in nearly 35% of neonatal admissions in India while different hospital-based studies in Nigeria documented between 2.6 and 30% [5–8]. Furthermore, Ekure et al [9] reported that HIE accounted for nearly 39% of perinatal mortalities at a tertiary hospital in Lagos, South-Western Nigeria. HIE can be mild, moderate or severe. However, the majority (about 90%) of cases of HIE that present to hospitals in Nigeria were moderate to severe [10]. The morbidity and mortality from HIE increases with increasing severity [10].

Survivors of moderate/ severe HIE have a high risk of developing severe cognitive and/or motor impairment, seizure disorders, deafness, and vision loss [11, 12] Neurologic abnormality at discharge is a strong predictor of long-term neurodevelopmental delay [13]. Many biomarkers of neurological damage resulting from asphyxia have been identified and investigated [14, 15]. Biomarkers such as nucleated red blood cells (NRBC) has been demonstrated to be markedly elevated in asphyxiated newborns and can be useful in predicting adverse neurological outcomes [13–15]. Inflammatory cytokines such as Interleukin-6 (IL-6) have been shown to accumulate early in asphyxia [16, 17]. Chiesa et al. [18] reported that IL-6 concentrations were more than 300-folds in babies with HIE as compared to normal infants. Furthermore, Creatinine kinase BB (CK-BB) has been shown to predict HIE early as its rise occurs in the first hours after brain injury [19].

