### Statistical analysis

Statistical analysis will be performed using Stata version 16.0 (Stata Corp, USA) statistical software after importing the data from the Excel spreadsheet. Descriptive statistics will be computed for socio-demographic characteristics and expressed as frequency tables and charts. Continuous variables that are normally distributed will be expressed as mean ± standard deviation (SD) while non-normally distributed continuous variables will be expressed as median and interquartile range (IQR). Association between categories of HIE and NRBC/100WBC will be tested using Students t-test. Also, the association between the grades of HIE and the degree of neurodevelopmental impairment will be conducted using the Pearson’s Chi-square. Pearson’s Chi-square will be used to compare the Gross motor function among the categories of HIE. Time to discharge, time to death and time to achieving major neurological milestones will be evaluated using the survival analysis techniques. Kaplan Meir’s plot and Cox proportional hazard regression modelling will be conducted with severity (moderate or severe) of HIE as a primary explanatory variable. At the end-point, after 2 years of follow-up, the association between intervention arm and the end point parameters will be assessed using univariable and multivariable logistic regression modelling. Two-tailed test of hypothesis will be assumed and a *P*-value < 0.05 will be taken as statistically significant level.

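### The Kaplan-Meier and Cox analyses are keyed on baseline HIE severity rather than randomised arm, so no stated analysis compares the time-to-event outcomes between EPO and control

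*Protocol article*

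**What the plan says.** All the relevant text is in the Statistical analysis section of the protocol article.

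- Survival methods: "Time to discharge, time to death and time to achieving major neurological milestones will be evaluated using the survival analysis techniques". The next sentence fixes the explanatory variable for the Kaplan-Meier and Cox work: "Cox proportional hazard regression modelling will be conducted with severity (moderate or severe) of HIE as a primary explanatory variable".
- t-test: "Association between categories of HIE and NRBC/100WBC will be tested using Students t-test".
- First chi-square test: "the association between the grades of HIE and the degree of neurodevelopmental impairment will be conducted using" Pearson's test.
- Second chi-square test: "Chi-square will be used to compare the Gross motor function among the categories of HIE".
- Logistic regression, after 2 years of follow-up: "the association between intervention arm and the end point parameters will be assessed using univariable and multivariable logistic regression modelling".

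The aims are set elsewhere in the article. The null hypothesis is that EPO affects neither immediate nor long-term outcome. The second specific objective compares neurological outcomes under EPO with those under routine care, in the neonatal period and at 6, 12, 18 and 24 months. Secondary outcome measures lists time to discharge alongside survival at discharge.

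**The concern.** HIE severity is a baseline characteristic that was not randomised. A Cox model or Kaplan-Meier plot built on it shows how prognosis differs between moderate and severe disease. It does not show whether EPO shortens the time to discharge, delays death or brings milestones forward. An analyst who follows the section literally would report hazard ratios for severity and none for treatment.

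The gap falls on the early outcomes, which the null hypothesis names explicitly. If a between-arm survival analysis is added only after unblinding, it will look post hoc, because the published plan named a different explanatory variable.

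**Working it through.** **Step 1. Which variable does each stated analysis use?**

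| Analysis | Outcome | Grouping or explanatory variable named |
|---|---|---|
| t-test | NRBC/100WBC | HIE category |
| Chi-square | Degree of NDI | HIE grade |
| Chi-square | Gross motor function | HIE category |
| Kaplan-Meier and Cox | Times to discharge, death, milestones | HIE severity |
| Logistic regression after 2 years | End-point parameters | Randomised arm |

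Four of the five name severity and one names arm.

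**Step 2. Is the primary comparison affected?** The primary outcome is a binary composite of death or NDI, and a logistic model on arm suits it. The stated sample size was derived for the same comparison. Inputs from Sample size and power calculation: control rate 0.65, relative risk 0.6, 80% power, 10% loss. Two-sided 0.05 comes from Statistical analysis and 1:1 allocation from Study design.

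- EPO rate: 0.65 × 0.6 = 0.39. Difference 0.26, mean rate 0.52.
- n per arm = [1.960 × √(2 × 0.52 × 0.48) + 0.842 × √(0.65 × 0.35 + 0.39 × 0.61)]² / 0.26²
- = (1.960 × 0.7065 + 0.842 × 0.6822)² / 0.0676 = 56.8, rounded up to 57.
- Allowing for loss: 57 / 0.90 = 63.3, rounded up to 64 per arm, **128 in total**.

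The plan's figure reproduces exactly. With 57 evaluable per arm the power is 80.2%. The choice of Cox variable changes none of this.

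**Step 3. Can the logistic regression stand in for the survival analyses?** It cannot do so for timing. A binary model at 2 years compares whether an event has occurred, not when. For discharge the loss is almost complete: once the hospital stay is over, discharge status records little beyond survival to discharge. For death and milestones, the model can compare proportions if they count as end-point parameters, but it cannot compare times.

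**Step 4. Can it cover NDI and gross motor function?** In part. Primary outcome measures includes GMFCS of 2 or more and delayed milestones among the NDI components, so NDI as a yes/no status by arm can fall under the logistic model. The graded outcomes, degree of NDI and GMFCS level, have a stated test only by HIE grade.

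**Step 5. Do the aims call for the missing comparisons?** The null hypothesis covers immediate outcome without restriction, so it reaches discharge and death. The second objective concerns neurological outcomes, so it reaches milestones, NDI degree and GMFCS level. Time to discharge is also a declared secondary outcome.

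The documents give no hazard ratio or event count, so the power of a between-arm Cox comparison cannot be derived from them.

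**The case against.** The case for leaving the text alone has real substance.

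- **The confirmatory test is by arm.** This stands. A reader might infer that the trial as planned never tests EPO against control. The documents do not support that, because the logistic regression on arm serves the primary composite.
- **Gross motor function is not wholly missing by arm.** This also stands. A reader might infer that the EPO effect on GMFCS is never estimated. GMFCS of 2 or more is a component of NDI, and the plural reference to end-point parameters can be read to include it. What is unclear is the comparison of GMFCS level and NDI degree.
- **The by-severity analyses are legitimate.** This stands. The NRBC t-test relates a marker sampled at admission to HIE category and was not meant to test treatment. The Background does say that "The morbidity and mortality from HIE increases with increasing severity", from which a reader might infer that these analyses only repeat what is known. Yet the sample size section reports a paucity of recent local data on mortality and impairment, and no report of 2-year impairment prevalence. The analyses by HIE grade also fit the first objective, on the spectrum of morbidity.
- **Only time to discharge is a declared time-to-event outcome.** This is correct, and it is the firmest part of the point. Times to death and to milestones appear only in the analysis section.
- **Severity is called a primary variable, not the only one, and covariate lists are usually left to an analysis plan.** The wording does not exclude arm from the Cox model, but nothing says that arm enters. Nor is this detail left open: the text names an explanatory variable, and a plan that follows it would carry severity forward in that role.

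**Conclusion.** The point holds as a should-fix affecting secondary analyses. For three of three time-to-event outcomes, the only stated analysis takes baseline severity as its named explanatory variable, and no stated analysis estimates the effect of EPO on them. For degree of NDI and GMFCS level, the between-arm comparison is not clearly specified. The primary comparison and its sample size are intact.

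This rests on reading the section as written. If a fuller protocol or analysis plan, finalised before unblinding, already puts arm into the survival models, the remaining step is to bring the published text into line with it.

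**What to change.** 1. Name the randomised arm as the primary explanatory variable in the Kaplan-Meier plots and Cox models for discharge, death and milestones, with HIE severity as a covariate or stratum. The article describes simple randomisation, so severity may differ between arms by chance, and adjusting for it is sensible.
2. State a between-arm comparison of NDI degree and GMFCS level, adjusted for or stratified by severity.
3. Keep the by-severity analyses, including the NRBC t-test, and label them descriptive or prognostic.

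The cost is a wording change to one section, using data already collected. It needs no extra patients and leaves the 128 unchanged. It should be made before any unblinded analysis.

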## Discussions

HIE is prevalent in resource-poor countries. The absence of facilities for therapeutic hypothermia reduces the chances for survival and increases the risk of morbidity. The use of EPO has been shown by several trials conducted in newborn infants with HIE to be beneficial in reducing morbidity and improve neurodevelopmental outcome even in infants that did not receive therapeutic hypothermia [40]. The previous studies did not document significant adverse reactions with the use of the drug. The systematic review by Garg et al [39] concluded that EPO improves neurodevelopmental outcome and is quite safe in neonates with hypoxic-ischaemic encephalopathy. More evidence to strengthen these findings will enhance its continued use. This study is expected to provide further evidence to either support or disprove the usefulness of Erythropoietin as a sole agent in the treatment of HIE. Either way, it will aid decision making and counselling of parents by newborn care providers treating infants with HIE, especially in resource-limited environment. Moreover, evidence-based, cost-effective measures that will not only curtail mortality but will also enhance the quality of life of survivors of HIE should be encouraged.

## Data Availability

Data sharing does not apply to this article as no datasets were generated or analysed during the current study.

## Abbreviations

PA: Perinatal asphyxia
HIE: Hypoxic ischaemic encephalopathy
EPO: Erythropoietin
LUTH: Lagos University Teaching Hospital
LMIC: Low and middle-income countries
NRBC: Nucleated red blood cells
CK-BB: Brain Creatinine kinase
IL: Interleukin
HT: Therapeutic Hypothermia
CPAP: Continuous positive airway pressure
WBC: White blood cell
MDAT: Malawi Developmental Assessment Tool
USS: Ultrasound
GMFCS: Gross Motor Function Classification System
WHO: World Health Organization
GCP: Good Clinical Practice
IQR: Interquartile range
HREC: Health research and ethics committee
